#### Physical activity and sleep

Physical activity and sleep patterns are determined by ActiGraph GT3X+accelerometer (ActiGraph, Pensacola, Florida, USA) for 7 days/8 nights immediately following the prebaseline visit and again for 7 days/8 nights during the third week of the intervention. During these wear-periods, a self-administered sleep-log to assess bedtimes is also obtained.

#### Gut microbiota analyses

Microbiota composition will be determined on faecal samples collected within 24 hours prior to the clinical investigation days at baseline and week 10. These samples are not used in the cluster assignment but are collected and stored for future analyses.

#### Data management

Study investigators have access to the data collection forms and protocols using a secure shared drive. All collected data are pseudoanonymised and participants are identified only by a study ID number on documents and on electronic databases, with personal identifiers kept separately under strict access control, limited to investigators and study staff directly involved in data collection and entry. All biological specimens sent to the consortium partners are pseudoanonymised and encrypted. On completion of the study, data will be stored in a password-protected database, accessible only by study investigators, in anonymous form for a minimum of 10 years.

#### Data monitoring

As the intervention risks to participants are minimal, a Data and Safety Monitoring Board was not deemed necessary. However, in case of unexpected adverse events during the study period, these are recorded and brought up to the principal investigator for appropriate decision-making. We did not plan to conduct interim analysis for safety as we did not anticipate any serious adverse events that would require trial termination.

#### Power and sample size calculation

To detect a difference in body fat mass change of 1.25 kg between the two intervention groups with 80% power at a two-tailed level of significance of 0.05, assuming a SD of 2.0 kg, a sample size of 41 per group (ie, personalised vs control) is needed, that is, a total sample size of 82 completers. To allow for an anticipated 18% dropout rate, 50 subjects per group would need to be recruited (total n=100). The expected difference in fat mass between groups (1.25 kg) and the associated SD (2.0 kg) were based on values calculated from the raw data of the SHOPUS study.^47^ In that study, we reported on body weight and fat mass during a 6-month dietary intervention in subjects with BMI of 22.6–47.3 kg/m^2^. To conduct power calculations for this study, we extracted raw data from the SHOPUS study that were most representative of the current subjects and intervention duration. Accordingly, we selected those SHOPUS participants with BMI ≥27 kg/m^2^ and elevated waist circumference (males >94 cm; females>80 cm) which represented more than 67% of the total study population (n=145) and assessed their body weight and fat mass at 12 weeks; this was an interim time point of the SHOPUS study (not published in the original paper),^47^ which was the closest to the 10-week time frame of the current intervention.

### Statistical analysis

Data analysis will be conducted using IBM SPSS Statistics version 28 (IBM Corp., Armonk, NY, USA) and R. Before statistical analyses are conducted, all continuous variables will be tested for normality and homogeneity of variance. For our primary objective, differences in fat mass from baseline to end of trial (V3 minus V2) between the two intervention groups (personalised vs control) will be compared by means of linear mixed models with time and randomisation group as main effects, a time-by-group interaction, and adjusting for potential confounders (eg, sex, age and BMI at baseline) as necessary. If significant interactions emerge, post hoc testing will be used to evaluate effects within the metabolic clusters. LMMs are able to handle possible imbalances between groups in case of missing values in a single response variable.

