### Randomisation and concealment

Prior to the intervention, all participants are stratified by metabolic cluster (oxidative stress; inflammation; carbohydrate metabolism; lipid metabolism; microbiota-generated metabolites) and then randomly assigned to either the control or the intervention group, in a 1:1 allocation ratio, by using a computer-generated randomisation sequence with random permuted block sizes of two subjects within each stratum. The person responsible for randomisation and generating the code does not take part in the inclusion and examination of study participants.

In order to maintain blinding, the clustering results for all participants are shared by Eurecat before the baseline visit (V2) with a member of the staff at NEXS (not through the platform) who is only responsible for randomisation. Consequently, the allocation information is incorporated into each participant’s profile in the PREVENTOMICS platform after passing back the randomisation information to Eurecat by the staff member at NEXS. However, this field is visible only to SimpleFeast (Denmark) and ONMI (The Netherlands; behavioural change technology, https://www.onmi.design/) user accounts for appropriate delivery of food and behavioural prompts. The profile includes the assigned group (personalised or control) and cluster, in addition to relevant recommendations to each subject. The local team of investigators at NEXS as well as participants are therefore unaware of the clustering and the randomisation of the participants as this field is hidden from their user account. Moreover, the statistical analyses of the main outcome variable will be conducted without breaking the code for the intervention treatment until the primary analyses have been finalised.

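### The primary model does not prespecify the randomisation stratum (metabolic cluster), so the test is conservative to the extent that cluster predicts change in fat mass

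*Protocol article*

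**What the plan says.** Under Randomisation and concealment, "all participants are stratified by metabolic cluster" before allocation. The arms are to be equal in size, and the sequence uses "random permuted block sizes of two subjects within each stratum". There are five clusters.

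Under Statistical analysis, the change in fat mass between V2 and V3 is compared by "linear mixed models with time and randomisation group as main effects, a time-by-group interaction". The choice of covariates follows an open rule: "adjusting for potential confounders (eg, sex, age and BMI at baseline) as necessary". Cluster enters the analysis at one point only: "If significant interactions emerge, post hoc testing will be used to evaluate effects within the metabolic clusters".

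Under Power and sample size calculation, the target is given as "difference in body fat mass change of 1.25 kg between the two intervention groups with 80% power"; the test is two-sided at 5%. The SD is 2.0 kg, with 41 completers per group and 100 recruited to allow for 18% dropout. The SD carries no stated reduction for cluster or any other covariate.

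**The concern.** Blocks of two within each cluster make the arms nearly identical in cluster mix. If clusters differ in average fat loss, that variation hardly touches the treatment difference, so the estimate is more precise than an unstratified design would make it. A model that leaves cluster out cannot see this. It counts the between-cluster variation as residual noise, reports too large a standard error and tests below its nominal level.

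The covariate rule makes this more likely. It asks whether a variable needs adjustment as a confounder. Cluster is balanced by design, so it will not look like one. A stratification factor belongs in the model because the design balanced it, not because it turned out unbalanced.

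At stake is efficiency: somewhat wide confidence intervals and some forgone power. The same applies to the secondary outcomes. Several of them (lipids, glucose, insulin, CRP, IL-6, leptin, adiponectin) are also among the markers that define the clusters, so cluster may plausibly predict their change, although the documents do not quantify this either.

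**Working it through.** **Inputs.** From the power section: Δ = 1.25 kg, σ = 2.0 kg, two-sided α = 0.05, power 80%, 41 completers per group, 18% dropout. From the randomisation section: five strata, blocks of two. Assumed: R², the share of the variance of fat-mass change explained by cluster, from 0 to 20%.

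**The plan's own figure.** n per group = 2σ²(z₀.₉₇₅ + z₀.₈₀)²/Δ² = 2 × 4 × (1.960 + 0.842)²/1.5625 = 40.2, rounded up to 41. Recruitment: 82/0.82 = 100. Both reproduce. Power at 41 per group is 80.8% by the normal approximation and 79.8% by the noncentral t with 80 df.

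**Formulas with balanced strata.**
- Standard error reported without cluster: 2.0 × √(2/41) = 0.442 kg.
- True standard error under stratification: 0.442 × √(1 − R²).
- Type I error without cluster: 2 × [1 − Φ(1.96/√(1 − R²))].
- Power without cluster: Φ((1.25 − 1.96 × 0.442)/true SE).
- Power with cluster: Φ(1.25/true SE − 1.96).

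| R² | True SE (kg) | Reported/true SE | Type I error without cluster | Power without | Power with |
|---|---|---|---|---|---|
| 0 | 0.442 | 1.00 | 5.0% | 80.8% | 80.8% |
| 5% | 0.431 | 1.03 | 4.4% | 81.4% | 82.7% |
| 10% | 0.419 | 1.05 | 3.9% | 82.0% | 84.7% |
| 20% | 0.395 | 1.12 | 2.8% | 83.5% | 88.6% |

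**Simulation with dropout.** 100 participants were randomised in blocks of two within five strata, 18 were dropped at random, and the change was analysed with and without stratum indicators. There were 6,000 replicates per setting; Monte Carlo error is about 0.5 points for power and 0.3 for type I error. Equal strata were 20% each; unequal strata were 40/25/15/12/8%.

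| R² | Power without/with, equal strata | Power without/with, unequal strata | Type I error without cluster, equal/unequal |
|---|---|---|---|
| 0 | 79.4/78.9% | 79.9/79.0% | 5.7/4.9% |
| 5% | 79.8/80.6% | 80.7/81.2% | 4.6/5.1% |
| 10% | 80.2/82.8% | 80.8/83.4% | 4.1/4.2% |
| 20% | 81.7/87.3% | 82.0/87.5% | 3.3/3.2% |

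Dropout loosens the balance a little, so the effects are slightly smaller than the formulas give at 5%, but direction and order of size agree. Without cluster, power stays at about 80% or above throughout.

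**Which term is needed.** With two visits and complete data, the time-by-group contrast depends only on each person's change. A cluster main effect is the same at both visits and cancels. In one simulated data set (82 complete participants, R² = 20%), the standard error of time × group was 0.4266 with no cluster term, 0.4266 with a cluster main effect, and 0.3953 with cluster and cluster × time.

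**The case against.** The strongest reply is that the loss is conditional. It requires cluster to predict change in fat mass, and no section gives a figure for that. The article argues that matching diet to cluster helps, which is not the same as saying that some clusters lose more fat. The larger R² values are demanding: with five equal, evenly spaced clusters, the extreme means differ by 4 × 2.0 × √R²/√2, which is 1.3, 1.8 and 2.5 kg at 5, 10 and 20%. The whole target effect is 1.25 kg. This stands. It favours the lower end of the range, without excluding the upper.

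Second, the covariate list is given by example, and this is a condensed article. A reader might infer that the plan excludes cluster; the text does not support that. What does stand is that the article sets out the model terms and a rule for adding covariates, that the rule would tend to pass over a balanced stratifier, and that cluster is given a post hoc role only.

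Third, a reader might infer that the trial is underpowered or its test invalid. Neither follows. The sample size rests on the unadjusted SD, so the unadjusted analysis delivers the planned 80%, and the error lies on the conservative side.

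Fourth, the local team is kept unaware of cluster, so adjustment needs a data transfer as well as a sentence. That also stands, but it is easily arranged.

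**Conclusion.** The point holds as a modest, conditional matter of efficiency. The design stratifies by cluster, and the stated primary model does not commit to using it. If cluster explains 5 to 20% of the variance of fat-mass change, the test runs at about 3 to 4.5% instead of 5%, and about 1 to 6 points of power are forgone relative to an adjusted analysis. If it explains nothing, nothing is lost. The estimate is unbiased, type I error is not inflated and the planned power is kept. The figures assume an SD of 2.0 kg, 41 completers per group, dropout unrelated to outcome, and an R² range that the documents neither give nor rule out. The change is still worth making, because it aligns the analysis with the randomisation at almost no cost.

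**What to change.** State that the metabolic cluster used for randomisation is a prespecified factor in the primary and secondary models, entered so that it acts on the change. Either include cluster and cluster × time in the mixed model, or fit an ANCOVA of V3 fat mass on V2 fat mass with group and cluster as factors. Say this explicitly, since adding cluster as a main effect alone would change nothing. Keep it apart from the covariates chosen according to need.

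The cost is 4 degrees of freedom (80 to 76 with 82 completers). If cluster is not predictive, power falls by about half a point, and by less than one point in every simulation run. The analyst must also receive the cluster field, which is hidden from the local team. This does not reveal treatment: with blocks of two, every cluster with at least two participants is represented in both arms.

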### Data collection and outcome measures

Data are collected at screening, prebaseline (V1), baseline (V2) and 10 weeks after initiating the intervention (V3) by using self-reported questionnaires, biological specimens, accelerometers and physical examinations conducted by trained local research staff in accordance with standard operating procedures (table 5). All primary and secondary endpoints are derived from measurements obtained at baseline (V2) and at the end of the intervention (V3). Measurements taken prebaseline (V1) were used for clustering assignment. Reminder text messages are being sent to the participants before visit days. It is expected that a high retention rate will be achieved due to the nature of the study.

**Table 5 T5:** Procedures and activities during the study period

	Screening visit (V0)	Pre-baseline visit (V1)	Baseline visit (V2)	End of trial visit (V3)
**Week**	−**20 to −13**	−**9 to −6**	**0**	**10**
**Visit day**	**0**	**1**	**2**	**3**
Informed consent	X			
Review of inclusion and exclusion criteria	X			
Medical history and examination	X			
Randomisation			X*	
Registration of medication and adverse events	X	X	X	X

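### The named covariates, if added as main effects to a two-visit mixed model, do not adjust the fat-mass contrast among completers, and chance imbalance in baseline fat mass is left uncorrected

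*Protocol article*

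**What the plan says.** The Statistical analysis section of the protocol article compares change in fat mass, V3 minus V2, between the two groups. It uses a linear mixed model with time and randomisation group as main effects and a time-by-group interaction, "adjusting for potential confounders (eg, sex, age and BMI at baseline) as necessary". It relies on the mixed model to cope with missing values. It does not say how the covariates enter.

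The section on data collection and outcome measures takes every primary and secondary endpoint from V2 and V3. Table 5 shows DXA at those two visits only.

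Randomisation is stratified by metabolic cluster (Randomisation and concealment). Cluster is not among the covariates named for the primary model.

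The section Power and sample size calculation states its target as follows: "To detect a difference in body fat mass change of 1.25 kg between the two intervention groups". Power is 80%, the test is two-sided at 5%, and the SD of change is taken as 2.0 kg. This leads to 41 completers per group (82 in all) and to 100 recruited, to cover 18% dropout.

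**The concern.** With two visits and a time-by-group term, the treatment effect is the difference between groups in mean change. Sex, age and baseline BMI are constant within a person. Added as main effects, they explain differences between people in the level of fat mass, not in its change.

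Baseline fat mass does not help either. It enters as the V2 response, and the group main effect lets the V2 means differ freely, so a chance difference in starting fat mass passes into the estimate.

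The reader is told that the primary comparison is adjusted, while for completers it would equal the unadjusted comparison of change. The design has little spare power, and predictors of fat loss that are already collected would go unused. The phrase *as necessary* also leaves the covariate set conditional, with no criterion stated.

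**Working it through.** **1. The plan's own figure.** Inputs from Power and sample size calculation: difference 1.25 kg, SD of change 2.0 kg, two-sided 0.05, power 80%, dropout 18%.

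- n per group = 2 × (1.960 + 0.842)² × 2.0² / 1.25² = 40.2, rounded up to 41.
- 41 / 0.82 = 50 per group, 100 in total.
- Power at 41 per group is 80.8% by the normal approximation and 79.8% by the noncentral t.

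The stated sample size is reproduced. It uses the SD of the raw change, with no reduction for covariates.

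**2. Why main effects cancel.** Write the model as Y(i,t) = b0 + b1·t + b2·G + b3·t·G + c·X + error, with t = 0 at V2 and t = 1 at V3. Subtracting gives Y(i,V3) − Y(i,V2) = b1 + b3·G + error, and c·X has gone. The level at V2 has its own free intercept and group coefficient, so it carries no further information about b3. With complete data, the estimate of b3 is the raw difference in mean change.

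**3. Check on simulated data, 82 completers, one set.** The covariate effects are invented, so only the pattern matters.

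| Model | Time-by-group (SE) |
|---|---|
| No covariates | −0.60481 (0.39451) |
| Sex, age, BMI as main effects | −0.60481 (0.39451) |
| Sex, age, BMI with covariate-by-time terms | −0.974 (0.383) |

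Random-intercept and unstructured covariance gave the same values. Main-effect adjustment moved only the group main effect (from −3.17 to 0.33 or 0.45), which is not the treatment effect.

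**4. With dropout.** Participants with V2 only stay in the mixed model, so cancellation is no longer exact.

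- In one illustrative set with 18% of V3 missing, main-effect covariates moved the estimate by about 0.04 kg and the SE by 0.4%.
- In a deliberately strong setting, missingness depended on BMI in opposite directions by arm (100 simulations per setting). The average shift was 0.05 kg with a random intercept (maximum 0.15) and 0.05 to 0.17 kg with unstructured covariance (maximum 0.37).
- The average SE in that setting was 0.43 to 0.44 kg with or without the covariates.

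**5. What effective adjustment could gain.** The residual SD becomes 2.0 × √(1 − R²). R² is an assumption; the article gives none.

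| R² | SD (kg) | Power at 41 per group, noncentral t | Normal approximation |
|---|---|---|---|
| 0 | 2.00 | 79.8% | 80.8% |
| 0.05 | 1.95 | 81.8% | 82.7% |
| 0.10 | 1.90 | 83.8% | 84.7% |
| 0.20 | 1.79 | 87.8% | 88.6% |

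**6. Baseline fat mass alone.** Assume equal variance at V2 and V3 and a baseline SD of 8 kg (not in the article).

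- The slope of change on baseline is −2.0² / (2 × 8²) = −0.031 kg per kg.
- R² = (0.031 × 8 / 2.0)² = 1.6%. Baseline SDs of 10 and 6 kg give 1.0% and 2.8%.
- A 1-SE chance imbalance is 8 × √(2/41) = 1.77 kg. It shifts the estimate by 1.77 × 0.031 = 0.055 kg, against an SE of 2.0 × √(2/41) = 0.44 kg.
- If heavier people lose markedly more, with slopes of −0.05 to −0.10, the shift is 0.09 to 0.18 kg. Those slopes imply that baseline fat mass explains (0.05 × 8 / 2.0)² = 4% to (0.10 × 8 / 2.0)² = 16% of the variance of change, so they cannot be combined with the 1 to 3% case.

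**The case against.** The text never says that the covariates are main effects only; it uses that term for time and group. Covariate-by-time terms are not excluded, and the list is introduced by *eg*, so baseline fat mass is not excluded either. The exact form of the model is also something a condensed article may leave to the analysis plan. This stands as far as it goes: the point rests on the natural reading of the stated model, not on a proven specification. However, the open list does not cure the problem, because any baseline variable entered as a main effect cancels in the same way.

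A reader might infer that the adjustment does nothing at all. That is exact only with complete data. The article expects 18% dropout, and then the estimate does move.

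A reader might also take V3 minus V2 as the model's response, which would leave one row per person and make the time terms impossible to fit. That is strained: the phrase describes the quantity compared, and the time factor implies two rows per person.

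On *as necessary*, the treatment code stays unbroken until the primary analyses are final, which limits result-driven choice of covariates. It does not remove it, since the contrast between coded groups can be seen. For completers, choosing among main-effect covariates could not change the estimate anyway. The wording matters once the covariates act on the change.

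Finally, a randomised comparison of change is valid without adjustment. That stands in full.

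**Conclusion.** The point holds in limited form. On the natural reading, the named covariates do not adjust the treatment contrast among completers. With about 18% of V3 missing they usually shift it only slightly, with larger shifts seen only under deliberately strong missingness, and they add practically no precision. Chance imbalance in baseline fat mass is not corrected, and the stratification factor is not a named covariate.

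The documents do not support reading this as bias or as an underpowered trial: the contrast is valid under randomisation, and the sample size is reproduced without any adjustment gain. The loss is forgone precision and uncorrected chance imbalance. Its size depends on an unstated R². For 5 to 20%, power would rise by about 2 to 8 percentage points. From baseline fat mass alone the gain may be small (1 to 3% of variance), with a shift of about 0.05 kg for a 1-SE imbalance, or more if heavier people lose markedly more.

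**What to change.** Rewrite the model sentence in Statistical analysis in one of two ways.

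- **ANCOVA:** V3 fat mass on group, V2 fat mass, metabolic cluster, sex and age.
- **Mixed model, to keep participants with missing V3:** V2 and V3 fat mass as responses, with the V2 means constrained equal between groups (no group main effect). Cluster, sex and age each enter with a covariate-by-time term.

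In either case, fix this covariate set in advance and delete *as necessary*. V2 fat mass takes the place of baseline BMI.

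No new measurements are needed. The cost is a few degrees of freedom: with 82 completers the unadjusted comparison of change has 82 − 2 = 80. The ANCOVA adds 1 (V2 fat mass) + 4 (five clusters) + 1 (sex) + 1 (age) = 7, leaving 73. Because the local team does not see the clusters, the analyst would need cluster as a coded variable.

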## ETHICS AND DISSEMINATION

The study has been approved by the Regional Committees on Health Research Ethics, Region Hovedstaden in Denmark (H-20029882) and is being conducted in accordance with the Helsinki Declaration. Any protocol amendments are submitted to the Research Ethics Board for approval and communicated to study participants and the trial registry once approved.

All personal data is being handled confidentially and stored in accordance with applicable law, GDPR and Danish Data Protection Agency. Participants received written and oral information on the study procedures, and only trained study-personnel provided information, monitored and attested signing of the informed consent form (online supplemental material 3). In addition, an optional GDPR consent to provide excess sample materials to study biobank was signed. The Research biobank has been approved by the Danish Data Protection Agency.

10.1136/bmjopen-2021-051285.supp3Supplementary data

A manuscript with the results of the primary study will be submitted for publication to an international, peer-reviewed journal, regardless of whether results are positive, negative or inconclusive in relation to the study hypothesis. Authorship eligibility will be based on the recommendations from the International Committee of Medical Journal Editors. On completion of the trial, and after publication of the primary manuscript, data requests can be submitted to the principal investigator at the Department of NEXS at the University of Copenhagen, Denmark.

